### Randomization and blinding

According to a stratified block randomization method, 240 patients are stratified by study center and randomly assigned to the high-dose group, low-dose group or placebo control group in a 1:1:1 ratio. The random sequence and the randomization list of each center will be generated by the independent specialist, using the PRCO PLAN function of the analysis system of SAS software (SAS, Cary, NC, USA). The independent drug administrator will assign numbered packs of study drugs to eligible patients in order by randomization list. The randomization sequence will be concealed in a lightproof sealed envelope, which will be kept by the leader and the Sponsor.

Participants, investigators and statisticians will be blind to the treatment allocation throughout the study. Test drugs and placebo will be identical in appearance, color and taste. All drugs are concealed in uniform packages with number labels. An emergency letter including the random sequence and assignment has been prepared in each center. In any emergency medical situation, such as serious adverse event or deteriorative condition, the unblinding process will be started after contacting the Sponsor and the primary investigator. The investigator should record the details of urgent unblinding and make sure the corresponding patient is excluded.

### Outcome measures

#### Primary outcomes

The primary outcome of the study is the time to fever relief, which is defined as the time (number of hours) from the first dose of the test drug until the axillary temperature drops by at least 0.5 °C. All patients are required to record their axillary temperature in the subject diary every 1 h within the first 6 h. Then, if the temperature is ≥ 37.3 °C, it should be recorded every 2–4 h, and if the temperature is < 37.3 °C, it should be recorded at 8 a.m. and 4 p.m. every day. If the temperature is < 37.2 °C and does not rise for 24 h, it does not need to be recorded. The investigator will check and collect the subject diary in which the data will be acquired and evaluated on the fourth day.

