### Inclusion criteria

The inclusion criteria are as follows: (1) meet the diagnosis of common cold according to Western medicine; (2) meet the diagnosis of CCHS according to traditional Uighur medicine; (3) fever and body temperature between 38 and 39 °C; (4) symptom presenting within 24 h; (5) age between 18 and 65 years and (6) voluntarily participate and provide signed informed consent.

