### Concomitant treatments and forbidden drugs

During the study, if the body temperature of a patient rises above 39.0 °C and/or the body temperature do not drop significantly at 48 h post administration, paracetamol can be used to bring down fever following the physician’s advice. Patients can continue their treatments for underlying conditions, such as diabetes mellitus or hypertension. Rescue treatment in the case of drug-related adverse events is also permitted in this study. Furthermore, considering the related impact on the study results, a patient with a drug-related adverse event may be withdrawn from this trial. All concomitant medications or treatments in the study must be recorded carefully in the case report form (CRF). Any other medication or therapy for common cold is not allowed during the study.

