##### Time to fever clearance

The time to fever clearance is defined as the time (number of hours) from the first dosing to the axillary temperature dropping to < 37.2 °C and no longer rising for 24 h.

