### Statistical analysis

The independent statistician will conduct the data analysis using SAS 9.4 software (SAS, Cary, NC, USA), in accordance with the statistical analysis plan for this trial. The primary analysis set for efficacy is the full analysis set (FAS) with an intention-to-treat (ITT) principle, in which all patients treated with at least one dose of study drug and who have a clinical observation record should be involved. According to an ITT principle, the last-observation-carried-forward (LOCF) imputation method will be used for missing data. Patients who fulfil the protocol without any major deviations will be included in the per-protocol set (PPS). And all participants who receive at least one dose of the study drug and for whom safety data are available will be included the safety set (SS). Baseline characteristics of all subjects will be analyzed using descriptive statistics for continuous variables and categorical variables. Primary efficacy will be analyzed by comparing outcomes among three groups. Outcomes among three groups will be compared using analysis of variance (ANOVA) and the Bonferroni method. Covariates designated as potential confounders will include age, gender, body mass index (BMI) and duration of symptomatic illness prior to enrollment. Time to fever relief, time to fever clearance and duration of all symptoms will be estimated by the Kaplan-Meier technique and compared by the stratified log-rank test. The improvement of TUM symptoms will be estimated by descriptive analysis for number and proportion of patients achieving clinical recovery. Prespecified subgroup analysis and sensitivity analysis involving covariance analysis will be used to evaluate the primary outcomes according to age and gender. In the multicenter trial, the Cochran-Mantel-Haenszel (CMH) test will be performed to analyze stratified variables. A two-sided *P* value <0.05 is considered as statistically significant.

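### The primary endpoint credits a temperature fall produced by permitted paracetamol as relief by study drug, which can dilute the drug-placebo difference by an amount the protocol does not let anyone derive

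*Protocol article*

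**What the plan says.** All references are to the protocol article.

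- **Primary outcomes.** The event is timed "from the first dose of the test drug until the axillary temperature drops by at least 0.5" °C. The definition does not mention antipyretics and does not require the fall to last.
- **Concomitant treatments and forbidden drugs.** Two triggers open rescue: "if the body temperature of a patient rises above 39.0 °C", with no time limit, and/or "the body temperature do not drop significantly at 48 h post administration". In either case "paracetamol can be used to bring down fever" on the physician's advice. Concomitant treatment must be entered in the case report form; no consequence for the analysis is stated.
- **Inclusion criteria.** Patients enter with "fever and body temperature between 38 and 39 °C", so the top of the entry range touches the first trigger.
- **Time to fever clearance.** The event is the temperature "dropping to < 37.2 °C and no longer rising for 24 h". It is also silent on antipyretics.
- **Statistical analysis.** "The primary analysis set for efficacy is the full analysis set (FAS) with an intention-to-treat (ITT) principle". Missing data are carried forward, and the per-protocol set drops major deviations. ANOVA with Bonferroni and a stratified log-rank test are both named for times to event.

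**The concern.** Paracetamol acts directly on the quantity that defines the primary event, and the patients who qualify for it are those whose fever is climbing or persisting. With the endpoint and the rescue rule as they stand, such a patient is scored as relieved soon after rescue. If study drug works, more of these patients should be on placebo. Their times are then shortened selectively and the difference shrinks. Unequal rescue between the two doses would also blur the dose choice, which is a stated aim of this phase II trial.

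This is more than a detail left to the analysis plan. The event definition is stated in full in the protocol, and as stated it gives this result.

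**Working it through.** **1. Does any other rule override the literal reading?**
- Carrying the last observation forward applies to missing values. A temperature taken after paracetamol is not missing.
- Permitted paracetamol is not a deviation, so the per-protocol set keeps these patients.
- The listed covariates (age, gender, BMI, prior symptom duration) and the subgroup and sensitivity analyses by age and gender do not involve rescue.
- Both triggers lie inside treatment: 3 days × 24 h = 72 h, and 48 h < 72 h.

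So nothing overrides it. Only patients rescued *before* their first 0.5 °C fall are affected.

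**2. The plan's own figure.** One-way ANOVA, 3 groups, alpha 0.05, η² = 0.06, N = 204. Noncentrality λ = N·η²/(1 − η²) = 204 × 0.06/0.94 = 13.02, which gives power 0.904. Then 68/(1 − 0.15) = 80 per group, 240 in total. The stated sample size reproduces. It contains no rescue input, so this point does not change it.

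**3. Size, by simulation (setting A).** None of these inputs is in the documents except 68 per arm, 72 h and alpha 0.05:
- exponential time to unaided relief, hazard ratio 1.7;
- a set share of patients crosses 39 °C at a uniform time in 0–24 h;
- 80% of the others are rescued if unrelieved at 48 h;
- paracetamol gives the 0.5 °C fall in 2 h;
- two-sided unstratified log-rank test, 1,000 runs per row.

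Three scorings are shown as literal / rescue counted as not relieved to 72 h / same trial without rescue. Differences are placebo minus active, with times capped at 72 h.

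| Placebo median | Set to cross 39 °C (placebo/active) | Rescued before relief | Power | Mean difference, h |
|---|---|---|---|---|
| 6 h | 0/0% | 0/0% | 86 / 86 / 86% | 3.5 / 3.6 / 3.5 |
| 12 h | 0/0% | 5/1% | 85 / 85 / 86% | 6.4 / 7.3 / 6.9 |
| 24 h | 0/0% | 20/7% | 79 / 82 / 84% | 8.3 / 11.0 / 10.4 |
| 12 h | 20/10% | 15/5% | 74 / 85 / 86% | 5.2 / 10.1 / 6.9 |
| 24 h | 40/20% | 41/18% | 33 / 89 / 85% | 3.9 / 15.4 / 10.7 |
| 12 h | 20/20% | 15/8% | 79 / 64 / 86% | 5.4 / 8.0 / 6.7 |
| 12 h | 10/20% | 10/8% | 85 / 45 / 85% | 6.2 / 5.5 / 6.9 |

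Across 18 such scenarios the literal mean difference was always below the no-rescue value, sometimes only trivially (3.50 against 3.52 h). The hazard ratio was not attenuated where rescue was negligible or where early crossing was set higher on active drug.

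**4. Setting B, Bonferroni level.** Hazard ratio 1.6, 68 per arm, alpha 0.05/3 = 0.0167 (three pairwise comparisons assumed), fall credited 1.5 h after rescue, everyone unrelieved at 48 h rescued, early crossing uniform over 0–24 h:
- 12 h median, 20/10%: literal 42%, no-rescue reference 59%. Repeat runs gave 42–45% and 59–63%.
- 24 h, 30/15%: literal 15%, reference 60%.
- 24 h, 48 h trigger only: literal 54%, reference 60%.
- 6 h, 10/5%: literal 57%, rescue-as-failure 58%.
- 12 h, 20/20%: literal 54%, rescue-as-failure 36%.

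**5. Fever clearance.** A patient rescued at 48 h cannot complete 24 h below the threshold before 48 + 24 = 72 h, when treatment ends. Clearance is therefore exposed mainly to early rescue. It was not simulated.

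**The case against.** The strongest reply has four parts.

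*Handling of rescue commonly belongs in the analysis plan, and counting outcomes regardless of rescue is a recognised reading of intention to treat.* This stands in part. The unshown plan may address it, and including all observed data is a legitimate strategy. It is a weak one here, because the permitted drug produces the event itself and the definition is already fixed in the protocol.

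*The size comes from assumed rescue rates.* This stands. A 0.5 °C fall is a low bar and readings are hourly for the first 6 h, so short relief times and little rescue before relief are plausible. The simulations also let paracetamol always succeed. If the fall is measured from the first-dose reading, entry at 38–39 °C puts the target at 37.5–38.5 °C. A patient above 39.0 °C would then need a fall of more than 0.5 to more than 1.5 °C.

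*Counting rescue as failure is not a neutral repair.* This stands. It creates a composite of relief and rescue. In setting A its mean difference exceeds the no-rescue value (10.1 against 6.9 h; 15.4 against 10.7 h), so its higher power partly reflects the assumed effect on escalation. With equal early crossing it loses power. Equal crossing is plausible, since a rise soon after the first dose may reflect illness course before any drug effect.

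*Direction.* A reader might infer that the drug effect will certainly shrink, or that the trial risks a false positive. The documents support neither. Dilution is expected if the drug works and rescue falls more on placebo, but no rescue rate is given. No inflation of false positives has been shown.

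**Conclusion.** The point holds on the text: the endpoint and the rescue rule together credit a paracetamol-induced fall as relief by study drug, and no stated rule prevents it. Dilution toward no difference is the expected consequence if the drug works and early rescue is commoner on placebo, and the dose comparison may blur in the same way.

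The main exposure is the 39.0 °C trigger, which can act early. The 48 h trigger alone costs little when most patients are relieved sooner, because those rescued still receive a late time. The simulated results show what could happen under their stated assumptions and are not forecasts for this trial.

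This should be fixed. Confidence is high on the text and low on the size.

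**What to change.** The clinical rescue rule stays as it is. The sections on concomitant treatments, primary outcomes and time to fever clearance must be reconciled in the endpoint wording and the analysis plan, before unblinding:

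1. Add to both definitions: *a temperature fall first reached after paracetamol or another antipyretic is not credited as fever relief (or clearance).*
2. Fix one primary scoring. One option is to count such patients as not relieved through the fourth-day visit. Either state the value that then enters ANOVA (for example 72 h) or name the log-rank test as the primary analysis, because censoring alone gives ANOVA no value.
3. Report as sensitivity analyses the as-recorded times and censoring at rescue.
4. Report rescue use by arm, with timing relative to the first 0.5 °C fall.

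The cost is wording; paracetamol use and temperatures are already collected. The statistical price should be stated openly. Rescue-as-failure makes the endpoint a composite and loses power if early rescue is equally common across arms. Censoring at rescue assumes rescue is unrelated to prognosis, which is doubtful when the triggers are rising or persistent fever. The sample size calculation needs no change on this account.

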#### Secondary outcomes

Secondary outcomes include the time to fever clearance, duration of primary symptoms and each symptom and change in TUM symptom score.

##### Time to fever clearance

The time to fever clearance is defined as the time (number of hours) from the first dosing to the axillary temperature dropping to < 37.2 °C and no longer rising for 24 h.

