##### Change in TUM symptom score

Currently, there is no grading evaluation standard for Uighur medicine. In this trial, the TUM symptom graded score system follows the *Guidelines for clinical research on new drug of chinese medicine* [20] (see Table 1). The primary symptoms are given a graded score (none = 0, mild = 3, moderate = 6, severe = 9) and the secondary symptoms are given a graded score (none = 0, mild = 1, moderate = 2, severe = 3). TUM signs will also be assessed, but not scored. The total score of TUM symptoms (including primary and secondary symptoms) will be summed at baseline (symptom score before treatment) and the fourth day (symptom score after treatment). The sum of all symptom scores is the cumulative TUM symptom score. The change in cumulative TUM symptom score is assessed by the percentage of symptom score reduction (PSSR), which is calculated according to the following formula:$$ \mathrm{PSSR}=\left(\frac{symptom\ score\ before\ treatment- symp\mathrm{t} om\  score\ after\ treatment}{symptom\ score\ before\ treatment}\right)\times 100\% $$

**Table 1 Tab1:** Symptom scoring system and TUM sign

TUM Symptoms	Score			
Primary	0	3	6	9
Fever	None	37.3 °C–37.9 °C	38 °C–38.5 °C	>38.5 °C
Nasal congestion	None	Mild	Moderate	Severe
Nasal discharge	None	Occasionally	Sometimes	Frequently
Sore throat	None	Dry throat with slight pain	Significant with obvious pain when swallowing	Sore and swollen throat with severe pain
Secondary	0	1	2	3
Cough	None	Occasionally in daytime	Occasionally day and night	Frequently day and night
Headache	None	Slight and occasionally	Slight and lasting	Severe and affecting working
Thirsty	None	Dry mouth	Moderate	Severe and drinking plenty of water
Sweating	None	Mild	Moderate	Severe
Sore limbs	None	Slight	Moderate	Severe
Cumulative symptom score	Primary symptom scores + secondary symptom scores			
TUM sign	Unscored			
Tongue body	□Red	□Others:		
Tongue coating	□Thick and yellow	□Others:		
Pulse condition	□Hard and rapid	□Others:		

*TUM* traditional Uighur medicine

Based on the therapeutic effect evaluation system, the improvement of TUM symptoms will be categorized into clinical recovery (PSSR ≥ 70%) and invalid (PSSR < 70%).

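### Temperature readings thin to twice daily below 37.3 °C, but fever clearance is timed at below 37.2 °C, so clearance is recorded late and on clock hours

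*Protocol article*

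**What the plan says.** The protocol article's Primary outcomes section sets the diary schedule. Patients "record their axillary temperature in the subject diary every 1 h within the first 6 h", whatever the value. After that, the frequency depends on the temperature. The closer schedule is kept for the higher values: "if the temperature is ≥ 37.3 °C, it should be recorded every 2–4 h". Under that level the diary thins to two fixed clock times: "if the temperature is < 37.3 °C, it should be recorded at 8 a.m. and 4 p.m. every day". Recording ends under a rule with a different cut-off: "If the temperature is < 37.2 °C and does not rise for 24 h, it does not need to be recorded".

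The section Time to fever clearance uses the same cut-off as the stop rule. It counts the hours "from the first dosing to the axillary temperature dropping to" a value under 37.2 °C. A persistence condition is attached, so the event in full is "the axillary temperature dropping to < 37.2 °C and no longer rising for 24 h".

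The Statistical analysis section names Kaplan-Meier estimation and a stratified log-rank test for this outcome. Nothing in the article explains why the switch to sparse readings sits 0.1 °C above the temperature that defines clearance.

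**The concern.** The schedule becomes sparse just before the event it has to time. A falling temperature must pass through 37.2 °C on its way to clearance. If a reading catches it there after the first 6 h, close follow-up stops although the event has not happened. The recorded time is then the next 8 a.m. or 4 p.m. reading below the cut-off, not a time close to the event.

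Treatment lasts 3 days and the diary is collected on the fourth day, so a delay of several hours is large against the observation window. Kaplan-Meier steps would tend to fall on clock hours, set partly by the time of day at which a patient was first dosed. That adds noise to the comparison of arms.

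A statistical analysis plan can choose a method that respects the gaps. It cannot recover readings that the diary never requested.

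**Working it through.** The plan gives no figure for the accuracy of clearance times, so there is none to reproduce. The sample size calculation does not depend on these cut-offs.

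**Step 1. Classify readings on a 0.1 °C scale, after the first 6 h** (inputs: Primary outcomes and Time to fever clearance).

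| Reading | Next reading required | Below the clearance cut-off? |
|---|---|---|
| 37.3 °C | in 2–4 h | no |
| 37.2 °C | next 8 a.m. or 4 p.m. | no |
| 37.1 °C | next 8 a.m. or 4 p.m. | yes |

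Only 37.2 °C is both not cleared and on the sparse schedule.

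**Step 2. Waiting time after a 37.2 °C reading.** The twice-daily schedule leaves gaps of 8 h (8 a.m. to 4 p.m.) and 16 h (4 p.m. to 8 a.m.), so the longest wait is 16 h. If the reading falls uniformly over the 24 h (an assumption):
- Mean wait = (8² + 16²) / (2 × 24) = 320 / 48 = 6.7 h.
- Share waiting more than 4 h = (4 + 12) / 24 = two thirds.
- Share waiting more than 8 h = (0 + 8) / 24 = one third.

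If it falls uniformly between 8 a.m. and 10 p.m. instead, the daytime gap contributes 8 h at a mean wait of 4 h and the evening 6 h at a mean wait of 13 h. The mean is (32 + 78) / 14 = 7.9 h, and (4 + 6) / 14 = 71% wait more than 4 h.

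These figures are conditional on a reading of exactly 37.2 °C and need no cooling model.

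**Step 3. Delay over all patients who clear.** This needs assumptions that the document does not supply:
- exponential fall from a start between 38 and 39 °C (the range in the inclusion criteria) to a settled level distributed N(36.8, 0.25);
- time constant of 5, 10 or 20 h;
- first dose between 08:00 and 18:00;
- frequent readings every 2 h or every 4 h;
- no measurement noise.

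Delay = first recorded reading below 37.2 °C minus the true crossing time, with 6,000 simulated patients per setting. Ranges run across the settings.

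| | Sparse below 37.3 °C (as written) | Frequent until below 37.2 °C |
|---|---|---|
| Mean delay | about 4–7 h | 0.9–2.0 h |
| 90th percentile | 9–14 h | under 4 h |
| More than 4 h late | about 32–67% | none |

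The share of clearing patients caught at 37.2 °C on the sparse schedule ranges from about 40% to 100%. It is highest when the fall is slow and the readings are close together.

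**Step 4. What alignment changes.** If frequent readings continued until the first value below the clearance cut-off, no uncleared patient would be on the sparse schedule. The longest wait for an uncleared patient would drop from 16 h to 4 h.

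**The case against.** Several points against the concern stand.

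- **The band is narrow and the early period is protected.** One value on a 0.1 °C thermometer is affected, and only after 6 h of hourly readings. Even so, a falling temperature passes through that value, and in the model a substantial share of patients are caught there.
- **The delay figures depend on the model.** The rate of fall, settled level and dosing hour are all assumed. The curve is smooth, with no daily rhythm and no rescue paracetamol. The 1–2 h comparison assumes perfect self-readings through the night, so it is a best case. The 16 h maximum needs none of this.
- **The schedule is the same in every arm, under blinding.** No direction of bias follows. A rough check of log-rank power (80 per arm, 25% faster fall, 4 h readings, 250 runs per setting, Monte Carlo standard error about 3 points) gave 0.27–0.44 as written and 0.34–0.50 with aligned readings. That fits a modest loss of precision and shows no more.
- **The primary outcome is untouched.** A fall of at least 0.5 °C uses neither cut-off.
- **Interval-censored analysis may already be in the unseen analysis plan.** It would use the sparse data correctly, but would not make them less sparse.

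A reader might also infer stronger claims that the document does not support:

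- **That patients settling at 37.2 °C fail to clear because of the mismatch, so part of the censoring is an artefact.** They fail because the endpoint requires a value below 37.2 °C. More frequent readings would leave them uncleared. An endpoint stricter than the threshold for frequent readings is a legitimate choice, and the stop rule agrees with it.
- **That clearance contradicts the fever item in Table 1, whose lowest graded band starts at 37.3 °C.** The score is taken only at baseline and on the fourth day, whereas clearance is a time-to-event measure with a 24 h persistence condition. They need not agree. That 37.2 °C scores zero is itself inferred, since the lowest category carries no number.

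**Conclusion.** The concern holds as a measurement fault in one secondary outcome. After the first 6 h, the recording rule and the clearance definition use cut-offs 0.1 °C apart, and a patient at 37.2 °C who has not cleared can go up to 16 h without a required reading. That follows from the text alone.

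The average effect rests on the cooling model: a mean delay of about 4–7 h as written, against 1–2 h at best with aligned readings. The consequence is late, clock-bunched clearance times in all arms and some loss of precision. The fault is worth correcting because the correction is cheap, but it does not threaten the trial's main conclusion.

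**What to change.** Reconcile the recording rule in Primary outcomes with the cut-off in Time to fever clearance, so that readings every 2–4 h continue until the first one below that cut-off and only then drop to twice daily. Neither the endpoint nor the Table 1 score needs redefining.

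For data already collected, and for patients on the present diary, analyse clearance as interval-censored between the last reading at or above the cut-off and the first below it. Specify this before unblinding. The same analysis handles two diary versions.

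The cost is a few extra self-readings per patient, some overnight, plus an amendment. Under Quality control, an amendment needs approval from the sponsor, the site investigators and the statisticians, and then goes to the ethics committee. Its reach is limited: recruitment began on 5 February 2018 and was due to end in early May 2019, and the article is dated 29 March 2019. A diary change would help only the last patients enrolled, so for most of the trial the interval-censored analysis is the usable part of the remedy.

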### Interventions

Binafuxi granules (batch Y170521) and placebo granules (batch Y170520) are manufactured by Xinjiang Yinduolan Uighur Medicine Co. Ltd., Xinjiang, China. The minimum effective dose of Binafuxi granules is 2.75 g. The Chinese herbal medicine placebo consists of 20-fold dilution of 2.75 g of Binafuxi granules and maltodextrin with the addition of artificial pigment and flavoring agents [19]. Patients in the placebo group will be administered placebo granules, which are almost identical to the Binafuxi granules in appearance, smell and taste. All test drugs are concealed in unified sealed packages and each package contains a 2.75-g dose. In each site, an independent drug administrator is responsible for dispensing, reclaiming, storing and recording of all test drugs. Patients in the high-dose group, low-dose group or placebo group will receive two packages of Binafuxi granules (5.5 g) twice daily, one package of Binafuxi granules (2.75 g) plus one placebo package (2.75 g) twice daily, or two placebo (5.5 g) twice daily, respectively. All test drugs will be dissolved in warm water and taken orally two times daily for 3 days. Throughout the trial, participants will be visited at baseline and on the fourth day post baseline (see Fig. 2). The study protocol complies with Standard Protocol Items: Recommendations for Interventional Trials (SPIRIT) (see Additional file 1). We will not regularly follow up all patients except in the case of an adverse event.

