##### Duration of all symptoms and each symptom

The duration of all symptoms is defined as the number of hours from enrollment to the time that all symptoms completely disappear. Each patient is required to record any change in symptoms in the subject diary. The investigator will assess the duration of all symptoms and each symptom.

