### Sample size calculation

Using “One-Way Analysis of Variance F-Tests using Effect Size” in PASS (version 15.0.5), we estimate the sample size with a significance level of 0.05. To our knowledge, no previous study has reported the effective size related to the time to fever relief in our target population (patients with common cold). Thus, we used η2 as an alternative measure of effect size, calculated by:

σm^2^ / (σm^2^ + σ^2^)

to estimate the sample size [21–23]. Generally, the effect size can be defined as follows: η^2^ = 0.0099 ≈ 0.01 is a small effect; η^2^ = 0.0588 ≈ 0.06 is a medium effect and η^2^ = 0.1379 ≈ 0.14 is a large effect [21–23]. In the study, we would like to determine the sample size required to detect a medium effect when the power is 0.90. Therefore, a total sample of 204 subjects (68 in each group) would be required. Assuming an overall 15% drop-out rate, 80 subjects should be recruited in each group. Finally, the total sample size is determined to be 240 patients.

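### Fever clearance requires 24 h without a rise, but once a patient is below 37.3 °C after hour 6 only 8 a.m. and 4 p.m. readings are scheduled, so a rebound confined to the 16 h gap is missed

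*Protocol article*

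**What the plan says.** Under Time to fever clearance, the protocol article counts hours from the first dose to "the axillary temperature dropping to < 37.2 °C and no longer rising for 24 h". This is the first-listed secondary outcome. The Statistical analysis section estimates it by Kaplan-Meier and compares arms with a stratified log-rank test.

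The temperature schedule behind it is fixed under Primary outcomes:
- All patients are to "record their axillary temperature in the subject diary every 1 h within the first 6 h".
- After that, "if the temperature is ≥ 37.3 °C, it should be recorded every 2–4 h".
- Otherwise, "if the temperature is < 37.3 °C, it should be recorded at 8 a.m. and 4 p.m. every day".
- Recording may end: "If the temperature is < 37.2 °C and does not rise for 24 h, it does not need to be recorded".

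Under Duration of all symptoms and each symptom, the article adds: "Each patient is required to record any change in symptoms in the subject diary". No temperature reading is tied to such an entry.

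**The concern.** The 24 h condition is there to separate a temporary dip from lasting clearance. The diary becomes sparse at the moment that condition starts to be tested. A patient at or above 37.3 °C gives 6 to 12 readings per 24 h, and a patient below it gives two. The stop rule then lets recording end once the condition appears to be met, so a false confirmation can also end the measurements that might have corrected it.

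This is a matter of data collection. No analysis plan can recover temperatures that were never taken. At stake is whether the clearance curves describe lasting clearance, or only clearance as seen in the morning and mid-afternoon.

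**Working it through.** The article gives no figure for this point to reproduce, and the sample size rests on other inputs and is unaffected. The inputs are the clearance definition and the diary rule. Rebound length L is an assumption.

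**Readings in the window.** Any 24 h window that opens after hour 6, with the patient staying below 37.3 °C at each reading, contains one 8 a.m. and one 4 p.m. reading. That makes two, or three with the qualifying reading. At intervals of 2 to 4 h, the count would be 24/4 = 6 to 24/2 = 12.

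**Uncovered time.** From 4 p.m. to 8 a.m. is 16 h, and 16/24 = 67%. In a window that opens between those times, the 16 h is split into two stretches but the total is unchanged. The other interval, 8 a.m. to 4 p.m., is 8 h.

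**Hypothetical patient.** First dose 10 a.m.; 37.0 °C at 4 p.m. (hour 6); 37.8 °C at 9 p.m., when no reading is required; 36.9 °C at 8 a.m.; 36.9 °C at 4 p.m. The recorded values are 37.0, 36.9 and 36.9 °C. None exceeds the one before and all are below 37.2 °C, so clearance is dated at 6 h. Had the 9 p.m. value been recorded, 6 h could not stand. Clearance would lie after hour 11 (10 a.m. to 9 p.m.).

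**Share of rebounds missed.** A rebound is missed if it starts and ends between two readings. With a uniform start over the clock, the share is [max(0, 8 − L) + max(0, 16 − L)]/24. For starts between 4 p.m. and 8 a.m., it is max(0, 16 − L)/16.

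| L (h) | Any start | Start 4 p.m. to 8 a.m. |
|---|---|---|
| 2 | (6 + 14)/24 = 83% | 14/16 = 88% |
| 4 | (4 + 12)/24 = 67% | 12/16 = 75% |
| 8 | (0 + 8)/24 = 33% | 8/16 = 50% |
| 12 | (0 + 4)/24 = 17% | 4/16 = 25% |
| 16 | 0% | 0% |

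If readings every 2 to 4 h continued through the window, no rebound of 4 h or longer would be missed.

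**Effect of evening readings.** One 8 p.m. reading splits the 16 h into 4 + 12. For L = 4 the night-start share falls from 75% to (0 + 8)/16 = 50%. Adding 10 p.m. gives 4 + 2 + 10 and (0 + 0 + 6)/16 = 38%. For L = 8 the shares are 50%, then 4/16 = 25%, then 2/16 = 13%.

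**The case against.** Several limits on the point are fair.

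- **The schedule is not always sparse.** The first 6 h are hourly, so a mid-afternoon first dose has its evening covered. Any reading of 37.3 °C or more restores readings every 2 to 4 h. A fever still present at 8 a.m. is caught. Only a rebound wholly inside the gap is lost.
- **The symptom diary gives partial cover.** Fever is a listed primary symptom, and Table 1 grades it from 37.3 °C, so a noticed return should be entered and seen when the diary is checked on the fourth day. But the entry requires no thermometer reading, and the clearance definition does not refer to it.
- **The definition itself is unclear.** Read strictly, any increase between readings breaks it, even one below 37.2 °C. The patient above satisfies both the strict reading and the reading that only the threshold matters.

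A reader might infer that the error favours the granules, because the drug is "taken orally two times daily for 3 days" and its effect could wear off between doses. The article gives no such temperature pattern, and all three blinded arms share the schedule.

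A reader might also infer that clearance times are always too short. That is not supported either. A reading of exactly 37.2 °C moves the patient to twice-daily readings without meeting the definition, so clearance can be dated up to 16 h late.

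Nor can a frequency be claimed. Simulated temperature curves can be made to give widely different answers. With an assumed daily half-range of 0.5 °C and a settling temperature of 36.8 °C, the ordinary daily peak is already 36.8 + 0.5 = 37.3 °C. The article gives neither quantity.

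**Conclusion.** The point holds in limited form. After hour 6, in a patient below 37.3 °C, the scheduled readings cannot verify the stated 24 h condition. They leave 16 of 24 h without a scheduled reading, and a rebound confined to that gap goes unrecorded, so clearance can be dated too early. The gap follows directly from the article's text. The missed shares also assume a rebound length and a uniform start time; they describe the rebounds that occur, not the proportion of patients affected.

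The supported consequence is misclassification and coarse timing of one secondary outcome. The definition of the primary outcome and the sample size are not touched. The overnight gap would remain even if the 37.2 and 37.3 °C thresholds were aligned.

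**What to change.** - **Primary outcomes (diary rule).** Until clearance is confirmed, add at least one evening or bedtime reading for patients below 37.3 °C, and a reading whenever the patient feels feverish.
- **Time to fever clearance.** Define it as the time of the first reading below 37.2 °C after which every recorded reading in the next 24 h, including an evening one, stays below one stated threshold aligned with the diary rule. This also settles what counts as a rise.
- **Patients enrolled without evening readings.** Describe their outcome as clearance based on 8 a.m. and 4 p.m. readings, and keep the two measurement regimes distinguishable in the analysis.

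The cost is one or two extra self-taken readings for about a day per patient, and somewhat later clearance times. Part of the night stays unobserved: with readings at 8 and 10 p.m., 10 h remain until 8 a.m. Timing limits the gain. Recruitment began in February 2018 and was due to finish in early May 2019, and the article appeared on 29 March 2019. A diary change made at publication would reach only the last weeks of enrolment, so for most patients the accurate description of the outcome is the part that can still be applied.
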